### IRB-Approved Protocol Changes During the Study

The protocol has been subjected to amendments twice, both approved by the IRB of the institution (Clinical Research Ethics Committee-IMIM).

The first amendment, submitted in January 2019, reported the following changes in the protocol:

Minor changes in the study advertisement sheet, participant information sheet, and IC formThe assessment of inclusion criteria was no longer done by the community moderators and was entirely assessed by self-reporting on online questionnairesAn increase in the required sample quantity to be sent to the laboratory from 30 to 50 mg by default, accepting exceptions depending on the substance potencyAddition of a key measurement timepoint at baseline before ingesting the substance.

The second amendment, submitted in November 2019, reported the following changes in the protocol:

Unblinding of the research team to the participant behavior and participationAddition of an optional timepoint for data collection in the reporting of the subjective effects of the reported substancesExtension of the duration of the study from 6 months to 1 year for each participantReduction of the required age for inclusion from 21 to 18 years.

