### Recruitment

Recruitment ads were sent to the moderators of the selected online communities after establishing bilateral communication with them, mainly to ask permission and explain the goals of the project. To maximize interest in participating in the study, the only focus was on establishing rapport with community leaders, as if they share their interest in the study, they will be able to transfer it to the rest of the community [31]. Each community moderator posted the research ad in the most appropriate way in their community after discussing it with the research team. Research ads were posted on all communities during the summer of 2019 (refer to Multimedia Appendix 3 for details). The recruitment was designed to be sequential until the designed sample size was reached or the study reached its duration limit.

The operational definition for online communities of people who use NPS has been adapted from the study by Barratt [21]:

Surface websites with at least 5 years of existencePresence of participation forums dedicated to discussing the use of NPSAt least weekly activity on the community forumThe use of pseudo-anonymity by community members to identify themselvesThe presence of official and analytical drug checking services in the community.

When the study design was completed (October 2018), there were 4 communities meeting the previously stated criteria [21]:

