The first mandatory step was to fill a sociodemographic and drug use history questionnaire (Q1). This questionnaire was available to each participant through a participant-specific link, which was sent by email once they were accepted. After that, participants were asked to fill the sample submission questionnaire (Q2), where information about the sample they intended to consume was asked. This questionnaire was then reviewed by the principal investigator and approved if the substance met the study criteria of being a new psychoactive substance. The samples that did not meet the inclusion criteria were not accepted, and the participant was notified by email. The sample submission questionnaire (Q2) was available to all accepted participants as a link on the platform. All the questionnaire answers were reviewed weekly by a member of the research team to communicate to the participant the acceptance of the sample and to mark them as valid or invalid data for later analysis.

If the sample was approved, the participant received a specifically generated sample code with the instructions to send a small amount of the sample (approximately 30 mg, usually below the psychoactive threshold) via traditional mail to the laboratory at the IMIM. The sample was analyzed there, and the result was sent back to the user, along with harm reduction advice when appropriate.

Meanwhile, the users could consume the substance whenever they decided, as the study was intended to be observational. However, most of the participants waited until they had the result of the laboratory analysis to proceed with the self-administration trial. The self-administration trial started with the users filling the drug effect baseline questionnaire (Q3a), and then, they consumed the reported substance and filled the drug effect questionnaire (Q3b) 24 hours after filling the baseline questionnaire (Q3a). The links to these questionnaires were available for all participants in the forum, and the veracity of the information was ensured by asking information only available to each participant, such as the sample code of the reported sample.

Study recruitment began in August 2019 and is still ongoing. In August 2020, the first participant concluded the 1-year follow-up.

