As it is an exploratory study, the data analysis procedures will be mainly descriptive statistics, to maximize an adequate visualization of the data collected within the minimum space. In addition, as there is no control group, statistical tests will be limited to potential comparisons to assess bias on the results, such as comparing data from participants who complete the study with participants who drop out or are excluded. However, no statistical corrections will be applied to adjust the representativeness of the sample, as this validation will be done by comparing the sociodemographics of the study sample with the characteristics of the population of psychonauts widely reported in the literature. Statistical tests might also be used to compare information from the initial questionnaire Q1 and the data from the follow-up questionnaire Q4. The nonparametric Wilcoxon signed-rank analysis will be used to perform a mean comparison of the quantitative data and the chi-square test for qualitative data. In addition, factor analysis will be attempted to study the relationship between all the visual analog scales used to assess the subjective drug effects.

The data analysis will focus on the outcomes of the participants who completed the study. Data entries containing evident errors or inconsistent information will be discarded, and the extent to which this might have impacted the results will be reported.

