## Results

The research protocol was approved by the IRB of the *IMIM* on December 11, 2018. Data collection started in August 2019 and was still ongoing when the protocol was submitted (September 2020), finalizing in October 2020.

Data analysis began in November 2020, and it is still ongoing. The authors expect to submit the first manuscript with preliminary results by the end of 2021.

From a total of 182 screened candidates, only 17 (9.3%) completed at least one self-administration trial, resulting in a total number of 64 self-administration trials. From these, 40 different substances were analyzed.

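### In the first collection period every one-year completer entered under the 21+ age rule, so the focus on completers and the completer-versus-dropout check are tied to entry date

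*Protocol article*

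**What the plan says.** The section on protocol changes states: "The second amendment, submitted in November 2019, reported the following changes in the protocol". Among those changes are a reduction "of the required age for inclusion from 21 to 18 years" and an extension "of the duration of the study from 6 months to 1 year for each" participant. The date of approval is not given.

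Both changes came after enrolment had started. The Recruitment section says "Research ads were posted on all communities during the summer of 2019". Study Procedures and Timeline says "Study recruitment began in August 2019 and is still ongoing", and adds: "In August 2020, the first participant concluded the 1-year follow-up". The Results section describes data collection as "still ongoing when the protocol was submitted (September 2020), finalizing in October 2020"; the Abstract calls this the end of the first collection period.

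The criteria box gives the current lower age limit of 18, without a date. Under Data Management and Statistical Analysis the plan says: "The data analysis will focus on the outcomes of the participants who completed the study". The same section names a comparison of completers with those who drop out or are excluded as an example of a test for bias. It rules out any statistical correction for representativeness and relies on a sociodemographic comparison with the literature.

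**The concern.** Eligibility and follow-up length both changed while people were being enrolled, but the analysis text treats the participants as one group. If only people who entered before the change could reach one year by the close of the first period, completion in that period is partly a matter of the calendar.

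Two things are then at stake. First, a description of one-year completers describes people recruited at 21 or older, while the criteria box suggests 18 or older. The comparison of Q1 with Q4, the 1-year questionnaire, has the same restriction. Second, anyone aged 18 to 20 in that period can appear only on the non-completer side of the bias check. A difference in age, or in anything that goes with age such as education or employment, could then arise with no real link between those characteristics and staying in the study.

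**Working it through.** **Inputs**
- Recruitment start: August 2019 (Study Procedures and Timeline).
- Second amendment: submitted November 2019, so in force on 1 November 2019 at the earliest (IRB-Approved Protocol Changes).
- Close of first collection period: October 2020, so between 1 and 31 October (Abstract; Results).
- Follow-up per participant: 6 months before the amendment, 12 months after it.
- Planning figures: 80 candidates, about 50% loss, 40 participants, one substance per month, 480 trials (Sample Size).

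**Step 1: the plan's own figure.** 80 × (1 − 0.5) = 40 participants, and 40 × 1 × 12 = 480 trials, as stated. With the 6-month duration it would be 40 × 1 × 6 = 240. The planning text therefore assumes the amended 12 months for everyone.

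**Step 2: latest entry for a one-year completer.** Close of period minus 12 months:
- 31 October 2020 − 12 months = 31 October 2019.
- 1 October 2020 − 12 months = 1 October 2019.

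The entry window for one-year completers is thus August to October 2019.

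**Step 3: earliest completion under the amended rules.** 1 November 2019 + 12 months = 1 November 2020, which is 1 day after a 31 October close. 30 November 2019 + 12 months = 30 November 2020, which is 60 days after a 1 October close. For a November start of the new rules the shortfall is 1 to 60 days; a later approval makes it longer.

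**Step 4: longest follow-up open to a post-amendment entrant at 31 October 2020.**
- Entry 1 November 2019: 365 days / 30.4375 = 12.0 months.
- Entry 30 November 2019: 336 days / 30.4375 = 11.0 months.

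The first case is the only near miss. Because 2020 was a leap year, 365 days is one day short of a calendar year. Someone admitted on 1 November 2019 would meet a 365-day definition only if the amendment took effect that day and collection ran to 31 October.

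**Step 5: the two entry groups side by side**

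| Entry | Lower age limit | Duration at consent | One-year completion by October 2020 |
|---|---|---|---|
| August to October 2019 | 21 | 6 months | possible |
| After approval (November 2019 or later) | 18 | 1 year | not possible |

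Entrants between November 2019 and approval, if any, also fall under the 21+ rule, and they too could not reach a full year.

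**Step 6: consequences.** Among first-period one-year completers the share aged 18 to 20 at entry is 0%, whatever the population share. Among non-completers it can exceed 0%. Six-month completion, by contrast, can be determined for the early group: entry by 31 October 2019 plus 6 months is the end of April 2020, inside the period.

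No mean-age shift is calculated. The article gives neither an age distribution nor accrual by month.

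**The case against.** The strongest reply is that little in the study depends on one-year completion. Q0 and Q1 are filled in around entry, and Q1 is required of every accepted participant. The main outcome is the change from Q3a to Q3b within a trial. The plan sets inclusion in the analysis by complete and valid questionnaires; it says the analysis will focus on completers, not that it is limited to them, and it does not define completion. This stands. A reader might infer that the answer to who the e-psychonauts are is itself confined to people of 21 and over. The documents do not support that, because later entrants supply the same entry data.

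A reader might also call the age floor hidden. It is not: the article reports the change, its month of submission and its ethics approval, and a difference between the amendment list and the current criterion is no error.

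A reader might infer that people who finished 6 months and went no further are counted as dropouts. Nothing says that anyone stopped at 6 months or how such a person would be classified. At least one early recruit did go on to a full year.

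Nor is there support for a stated number of years by which mean age is wrong, or for cutting the literature comparison at 21. The literature group is described only as mainly young, with no such age limit.

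Finally, the scope is narrow. The exclusion holds for the first period only, recruitment is described as continuing, and the margin can be as small as a day. A 1-year questionnaire accepted about a month early could let in a November 2019 entrant. With 17 of 182 screened candidates (9.3%) completing any trial, subgroups will be very small. These limit the point, but they do not answer the confounding of the bias check.

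**Conclusion.** The point holds for the first collection period. One-year completers by October 2020 entered between August and October 2019, before the amendment could apply. They were therefore recruited at 21 or older, and no post-amendment entrant could be among them. The focus on completers describes a 21+ group for that period, and the comparison of completers with dropouts is confounded with entry date and age rule.

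This rests on two assumptions: a full 12 months of follow-up is required for completion, and the age rule in force was followed at each acceptance. The missing approval date does not weaken it.

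The size is certain in one respect only: 0% aged 18 to 20 among these completers. The effect on mean age, education or employment cannot be derived from the article, and whether anyone stopped at 6 months is unknown. In an exploratory, mainly descriptive study this calls for a correction to the analysis text. It does not invalidate the design.

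**What to change.** Amend Data Management and Statistical Analysis in three places.

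1. Describe the Q0 and Q1 characteristics for all accepted participants, not only completers, and show entry before and after the approval date of the second amendment. State that one-year completers of the first period were recruited at 21 or older.
2. Run the completer-versus-dropout comparison only among participants accepted early enough to reach their full follow-up by the data cut-off. Report those still in follow-up at the cut-off as administratively censored, not as dropouts.
3. For participants who consented under the 6-month duration, report 6-month and 1-year completion separately.

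The cost is wording and some extra table columns. Acceptance dates and ages should already be held, since the investigator accepted each participant after checking the age criterion. The drawback is smaller groups in tables that are already small, so the split should be shown descriptively and not tested.

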### Outcomes

The domains and measurements used in the study are based on previous laboratory studies, to maximize consistency in methodology and to eventually develop a validation study for this methodology. Multiple studies have shown that web-based data collection and traditional methods (eg, paper and pencil) result in equivalent conclusions, demonstrating the validity and reliability of online data collection for research [37,38].

Certain studies have been used as model references to select the measured outcomes [39-52]. However, new outcomes regarding the subjective effects of psychoactive substances have been added to balance the amount of positive and negative effects reported. The order of the questions was kept the same to facilitate reports to those participants who completed the same questionnaire multiple times. However, 3 questions to assess validity were present in both the Q3a and Q3b. More information about study outcomes, including assessed domains, chosen measurements, metrics, and time points, can be found in Multimedia Appendix 5.

### Data Collection

#### Questionnaires

The study data were collected using a Columbia University Q*ualtrics* license, a well-known questionnaire platform compliant with the guidelines to store sensible information about the research participants. The screening questionnaire (Q0) and the sociodemographic questionnaire (Q1) collected self-reported information about the participants’ medical and drug history, psychosocial situation, and beliefs and behaviors related to drugs.

The subjective effects of drugs were assessed via visual analog scales, using the same parameters used in most laboratory studies to determine the subjective effects of drugs. The main outcome was the difference in mm from the drug effect questionnaire (Q3b) at 24 hours (referring to the peak experience) and the baseline questionnaire (Q3a).

Each questionnaire also had at least one validity entry to be filled by the researcher directly using the *Qualtrics* database. There were no automated consistency or completeness checks before the questionnaire was submitted, other than the validation criteria for certain questions. For example, the question *sample code reported* could not be submitted if the answer was not a 5-digit number.

The participants could go back through the questionnaire, but once submitted, they could not change their answers. A summary of the answers was not displayed either before or after submission. Two options were available to change the participants’ answers if they were incorrect according to the participant or not valid according to the researcher. If the change was small, the researcher could just edit the participant response in the *Qualtrics* database according to the correct response provided by the participant using email or the platform’s private messaging system. If the changes were relevant, the researcher could mark the questionnaire as invalid and provide another link to the participant.

Public links to copies of the used questionnaires can be found in the references cited below:

Q0, screening questionnaire [53]: contained a total of 37 questionsQ1, sociodemographic questionnaire [54]: contained a maximum of 351 questions, with an expected average per participant of 50, due to adaptive questioning and questionnaire logicQ2, sample submission questionnaire [55]: contained a total of 21 questionsQ3a, baseline drug effect questionnaire [56]: contained a total of 12 questionsQ3b, drug effect questionnaire given 24 hours after drug administration [57]: contained a total of 39 questionsQ4, 1-year follow-up questionnaire [58]: contained a maximum of 351 questions, with an expected average per participant of 50, due to adaptive questioning and questionnaire logic.

The number of pages and items on each page were optimized automatically by *Qualtrics* software and varied according to the screen size used to answer. The possibility to answer the questionnaires comfortably from the smartphone was assessed as an essential by the research team.

#### Laboratory Analysis

Preliminary sample identification was performed by GC coupled to MS using an Agilent 7890B gas chromatograph coupled to a 5977A quadrupole mass spectrometer detector (Agilent). The gas chromatograph was fitted with a G4513A auto-sampler injector. Insert liners packed with salinized glasswool were used, and the injector and interface were operated at 280 °C. Samples were injected in split mode into a 0.25 mm film thickness (5% phenylmethylsilicone) column (HP-5MS, Agilent Technologies). Helium was used as the carrier gas at a flow rate of 1 mL/min. The oven temperature was initially maintained at 90 °C for 2 minutes and programmed to reach 320 °C at 20 °C/min. It was finally maintained at 320 °C for 9.5 minutes (total run time was 21.5 min). The mass spectrometer was operated in the electron impact ionization mode at 70 eV. To confirm the mass spectra, 4 libraries were used: the NIST/EPA/NIH Mass Spectral Library, Data Version: NIST 14; Searchable Mass Spectral Library Version 2.3 [59]; Searchable Mass Spectral Library Cayman Spectral Library [60]; and EC’s internal mass spectral library. Confirmation (when needed) was performed by liquid chromatography (LC) coupled to tandem MS (LC/MS/MS) using an Agilent 1100 series HPLC (high performance liquid chromatography) chromatograph (Agilent Technologies) and an Esquire 3000 plus mass spectrometer MRM (Bruker Daltonic GmbH). Chromatography was performed using a Poroshell 120 EC-C18 column (100 mm length×2.1 mm internal diameter; 2.7 mm particle size) at 30 °C. The mobile phases consisted of 1% formic acid and 1% formic acid in methanol. The following gradient elution was used: at time 0 minute, 15% B was changed to 90% B in 7 minutes, held for 1 minute, and changed back to the initial conditions in 1 minute. Before injection of the next sample, the column was re-equilibrated for 7 minutes. The flow rate was 0.35 mL/min. The electrospray source was operated in the positive ionization mode. Product ions that were obtained by collision-induced dissociation allowed the MS/MS to be operated in the multiple reaction monitoring mode. The dwell time was set at 0.25 seconds. The desolvation gas was nitrogen set at 365 °C and delivered at a flow rate of 9 L/min. The capillary voltage was 3.90 kV, and the collision gas was helium. The Bruker Compass Hystar system software Version 3.2-SR2 was used for instrument control and identification.

#### GRASP Forum

Secondary data about the participants’ discussions on the study platform were supported by a licensed *discourse* (Civilized Discourse Construction Kit, Inc) account and the software used to build the platform. *Qualtrics* (SAP Global Corporate Affairs) data were downloaded for analysis, which was conducted using the institutionally licensed Microsoft Excel from the IMIM and R (R Core Team), which is a free software environment for statistical computing and graphics that does not require a license.

As it is an exploratory study, the data analysis procedures will be mainly descriptive statistics, to maximize an adequate visualization of the data collected within the minimum space. In addition, as there is no control group, statistical tests will be limited to potential comparisons to assess bias on the results, such as comparing data from participants who complete the study with participants who drop out or are excluded. However, no statistical corrections will be applied to adjust the representativeness of the sample, as this validation will be done by comparing the sociodemographics of the study sample with the characteristics of the population of psychonauts widely reported in the literature. Statistical tests might also be used to compare information from the initial questionnaire Q1 and the data from the follow-up questionnaire Q4. The nonparametric Wilcoxon signed-rank analysis will be used to perform a mean comparison of the quantitative data and the chi-square test for qualitative data. In addition, factor analysis will be attempted to study the relationship between all the visual analog scales used to assess the subjective drug effects.

The data analysis will focus on the outcomes of the participants who completed the study. Data entries containing evident errors or inconsistent information will be discarded, and the extent to which this might have impacted the results will be reported.

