### Sample Size

In the most recent review consulted by the authors, the sample sizes reached with web-based questionnaires in people who use illicit drugs ranged from 80 to 9867 [36]. The expected losses while filling these types of questionnaires are about 50% of the sample, but the authors have not found other online longitudinal studies including questionnaires like this one. According to the aforementioned review, the authors expected 80 candidates as the best possible estimate to achieve 40 final participants. Assuming that each participant takes one NPS every month during the duration of the study, the expected number of registered self-administration trials of NPS would be 480. As the study has been designed as exploratory, the sample size could not be determined based on the needs to perform specific statistical tests.

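### Completers are to be compared with people who drop out or are excluded by statistical tests, with no effect estimate or interval; at roughly 40 v 40 a null test cannot show that the groups are alike

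*Protocol article*

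**What the plan says.** All the text is in the Methods of the protocol article.

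- **Role of tests (Data Management and Statistical Analysis).** The analysis is mainly descriptive. The article reasons from the lack of a control group that "statistical tests will be limited to potential comparisons to assess bias on the results, such as comparing data from participants who complete the study". Dropouts and excluded people form the other side of that comparison. No effect measure, interval or significance level is given for it.
- **Representativeness (same section).** "However, no statistical corrections will be applied to adjust the representativeness of the sample"; instead, the sociodemographics of the sample are set against published descriptions of psychonauts.
- **Analysis set (same section).** The focus is on participants who completed the study. Only complete and valid questionnaires are used, and the possible impact of discarded entries will be reported.
- **Numbers (Sample Size).** "The expected losses while filling these types of questionnaires are about 50% of the sample", and "the authors expected 80 candidates as the best possible estimate to achieve 40 final participants". The study is exploratory, and "the sample size could not be determined based on the needs to perform specific statistical tests".
- **Data flow (Study Procedures and Timeline).** Candidates fill in the screening questionnaire Q0 before the decision on inclusion. The sociodemographic and drug history questionnaire Q1 is sent only after acceptance.

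**The concern.** The question behind the comparison is whether results from completers can stand for those who were lost or turned away. The reassuring answer is that the groups are similar. A test of difference can give evidence that groups differ, but its failure to reach significance is not evidence that they are alike, least of all with small groups. A p-value also mixes the size of the difference with the number of people, whereas a reader judging bias needs the size.

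It matters here because heavy loss is expected and the analysis concentrates on those who stay. The first hypothesis is that e-psychonauts are functional and educated. Staying through a year of demanding online questionnaires could plausibly select for those traits, so attrition might itself push the data towards the hypothesis. If the contrast is reported only as test results, a reader cannot tell how large a difference remains possible.

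**Working it through.** **Inputs from the article**

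- 80 candidates, about 50% loss, 40 final participants (Sample Size).
- Non-completers: 80 − 40 = 40. This is inferred by subtraction; the article does not state a 40 v 40 comparison.

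**Assumed inputs**

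- Two-sided 5% level.
- A relevant difference of 0.5 SD; other sizes are shown below.
- An unpaired test. The rank test that the article names, the Wilcoxon signed-rank, is for paired data and may be meant only for Q1 against Q4. The unpaired t-test and the Mann-Whitney test are used here.

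**Step 1: the article's own figures.** 80 × (1 − 0.5) = 40 final participants. 40 × 12 monthly uses = 480, which matches "the expected number of registered self-administration trials of NPS would be 480". No power figure is stated, so there is none to reproduce.

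**Step 2: power at 40 v 40 for 0.5 SD.** By the normal approximation, power = Φ(d × √(n/2) − 1.96) = Φ(0.5 × √20 − 1.96) = Φ(2.236 − 1.960) = Φ(0.276) = 0.609.

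| Method | Power | Miss rate |
|---|---|---|
| Normal approximation | 0.609 | 39% |
| t-test | 0.598 | 40% |
| Mann-Whitney, 20,000 simulations, normal data | 0.577 | 42% |

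**Step 3: sensitivity to the assumptions**

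- Other differences at 40 v 40 (t-test): power 0.14 at 0.2 SD, 0.26 at 0.3 SD, 0.94 at 0.8 SD.
- A binary item, 50% v 70% at 40 v 40: power 0.45.
- A two-sided 10% level at 0.5 SD: power 0.723, miss rate 28%.
- Fewer usable non-completers, 0.5 SD (t-test): 0.53 at 40 v 30, 0.43 at 40 v 20, 0.28 at 40 v 10. Because only complete and valid questionnaires count, and people rejected at screening have no Q1, 40 v 40 is probably a best case.
- For 0.5 SD, 80% power needs 63 per group and 90% needs 85.

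**Step 4: what an interval would show.** The 95% half-width for a standardised difference is 1.96 × √(2/40) = 0.438 SD (0.445 with the t quantile). Even an observed difference of zero would leave differences up to about 0.44 SD open. For a proportion near 50% the half-width is 1.96 × √(2 × 0.25/40) = 0.219, or 21.9 percentage points.

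**The case against.** The strongest reply is that the article does not make the error. Four parts of it deserve an answer.

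- **A reader might infer that bias is assessed only by significance tests, or that this is the sole safeguard on generalisability.** The text supports neither. It limits tests to bias assessment; it does not limit bias assessment to tests. The same section plans descriptive statistics, a comparison with the literature and a report on discarded entries. What remains is narrower: tests are the method tied to the contrast between completers and the others. The literature comparison does not answer that contrast, since it sets the sample against an external population.
- **A reader might infer that a non-significant result will be taken as no bias.** No such rule is stated, nor any significance level. This stands as a risk of interpretation, and the fix closes it.
- **Intervals are detail for an analysis plan that is not shown.** Their absence alone would not be a finding. But the article does choose an instrument for this question, and the choice suits it poorly. The article does not rule out estimates and intervals, so the change is easy.
- **The study is exploratory and was not sized for tests.** True, and the article claims no power here. That favours estimates with intervals over p-values.

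It is also tempting to recompute from the Results: "From a total of 182 screened candidates, only 17 (9.3%) completed at least one self-administration trial". Those figures do not fit. At least one trial is not study completion, and the remaining 165 (182 − 17) are everyone else screened, who could include rejected candidates without Q1. Nor can a count of chance findings be built on the average of 50 Q1 questions: Q1 is adaptive, so participants see different items, and the article does not say that every item will be tested.

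**Conclusion.** The point holds in a limited form. The article names statistical tests for judging bias between completers and those who drop out or are excluded, without an effect estimate or interval. At about 40 v 40, power for a 0.5-SD difference is roughly 0.58 to 0.61. A non-significant result would therefore leave a moderate difference quite possible, and would not show that the groups are alike.

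The figures rest on a split inferred from the sample size text and on an assumed 5% two-sided level and 0.5 SD. The conclusion is not sensitive to these: smaller differences or fewer usable non-completers lower the power, and a 10% level still misses 28%. The change is worth making because the analysis focuses on completers. It improves how one comparison is reported and does not show that the planned results are biased.

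**What to change.** In Data Management and Statistical Analysis, replace the sentence on tests for bias with wording such as:

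> Completers and non-completers will be compared by standardised differences, or differences in proportions, with 95% confidence intervals. Q0 items will be used for people excluded at screening, and Q0 and Q1 items for accepted participants who drop out. A non-significant p-value will not be read as absence of bias.

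No similarity margin is proposed, because the expected numbers cannot support one. At 40 v 40, a ±20-point margin could not be met for a proportion near 50% even with an observed difference of zero, since the half-width is 21.9 points. A ±0.5-SD margin would require an observed difference within 0.5 − 0.438 = 0.062 SD. With no true difference and a standard error of √(2/40) = 0.224 SD, that happens with probability 2Φ(0.062/0.224) − 1, about 22%.

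The cost is a few sentences and one table, with no new participants or data. The downside is that the report will often have to say that moderate attrition bias cannot be excluded, which is what data of this size can support.
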